### 2.6. Endpoint Criteria

Participants are considered to have completed the experiment when they finish all treatments and assessments or withdrew from the experiment for any reason midway through.

### 2.7. Recruitment and Screening

In total, 60 PD patients will be enrolled from the Parkinson’s Disease and Movement Disorders Clinic of Ruijin Hospital in Shanghai. Subjects who have been clinically diagnosed with PD by two specialists independently are recruited and screened based on inclusion and exclusion criteria. Cognitive function assessed by Mini-Mental State Examination (MMSE) and a history of neurological disorders and treatment are the focus of screening. Additionally, a blood test and structural MRI should be performed to exclude patients with other unsuited conditions for the study.

### 2.8. Randomization and Blinding

To reduce measurement bias during subjective assessment, we adopt a randomized grouping and double-blind design. Participants are assigned into four arms in a 1:1:1:1 design according to a predetermined generated random number table generated by computer algorithm before the start of the entire experiment. The clinical assessments are scored by specialists not involved in the intervention and grouping, based on the coded and disordered video to ensure the objectivity and authenticity. All the patients are blind to treatment. The pseudo-stimulation coil looks exactly the same as the real iTBS coil and emits the same sound and vibration sensation during the stimulation process, but there is no actual stimulation effect. Coil replacement will be completed before the patient enters the treatment room, which ensures that subjects are unaware of the grouping. Specifically, iTBS operators are unblinded because they need to exchange coils to conduct both active and sham stimuli. Blinding will be evaluated by asking participants to guess group assignment at the end of the whole experiment.

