### 2.2. Study Design

NET-PD is a 2-year prospective single-center, double-blind, multi-arm, delayed-start, sham-controlled trial. The study is conducted in two stages—the pseudo-controlled and active-treatment stage—with each stage consisting of a 2-week intensive phase and a 12-week maintenance phase, for a total of 14 weeks. The intensive period involves daily or twice-daily iTBS (or pseudo-stimuli) per week, for a total of 10 or 20 sessions, and the maintenance period consists of 12 weeks of iTBS (or pseudo-stimuli) once or twice a day, 2 days a week, for a total of 24 sessions in the single-stimulation group or 48 in the double group. In stage 1 (pseudo-controlled stage), patients are randomly assigned to one of four intervention groups in a 1:1:1:1 ratio: early-start single iTBS group (A1), early-start double iTBS group (A2), delayed-start single iTBS group (S1), and delayed-start double iTBS group (S2). The early-start groups conduct active iTBS throughout, whereas the delayed-start groups use pseudo-stimuli in the first stage and start using iTBS in the second stage. The only difference between the single- and double-stimulation group is the number of sessions per day: once daily for the single group and twice daily for the double group. In stage 2 (active treatment stage), participants in A1 and A2 continue to receive the same iTBS protocol as the first stage, while those in S1 and S2 start to receive active iTBS. All patients are required to have a detailed follow-up clinical assessment and electrophysiology record at baseline, 2 weeks, 14 weeks, 16 weeks, and 28 weeks. MRI and peripheral blood are collected at baseline, 14 weeks, and 28 weeks (Figure 1, Table 1). Each patient will spend 7 months in this study and the total duration of the research will be approximately 2 years, from July 2022 (first in) to December 2024 (last out) (Figure 2).

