### 2.9. iTBS Intervention and Follow-Up

During iTBS, three consecutive 50 Hz pulses are embedded in 5 Hz pulses (200 ms interval). The pattern is then repeated every 10 s in 2 s stimuli followed by 8 s rest sequence, for a total of 600 pulses in each session. In this study, the NS5000 transcranial magnetic stimulator and accompanying devices manufactured by Wuhan Yiruide New Technology Ltd. are used for treatment and measurements. Like the placebo control group in drug experiments, the pseudo-stimuli group is the control group to the active iTBS group. Active and pseudo-stimuli are delivered by matched coils, and a special pseudo-stimuli coil with the same appearance and sound as the active coil will be used. Patients can hear the specially designed sound and feel the vibration during stimulation, but there is no actual stimulation effect. This ensures that subjects are unaware of the grouping. Based on previous results, iTBS intervention was well tolerated with only few subjects reporting discomfort or pain, and no pathological increases in cortical excitability or seizure activity recorded on EEG/EMG monitoring [24,25,26].

Throughout the intervention, patients are first instructed to sit stably and relax in a comfortable position. Before the first intervention, each patient’s resting motor threshold (RMT) should be measured, which is defined as the minimum stimulus intensity necessary to elicit an overt motor response in the abductor pollicis brevis for ≥50% of applied stimuli [27]. We deliver iTBS to the bilateral primary motor cortex (M1) at 100% RMT. Stimulation targets for bilateral M1 are localized according to individual MRI brain structure images under the visor2 ^TM^ neuro-navigated system (ANT Neuro Ltd., Hengrlo, The Netherlands). Subjects in each arm undergo two intervention circles, each composed in an intensive phase for 2 weeks, followed by a maintenance phase of twice-weekly sessions for 12 weeks. Each patient should be stimulated at the same time of day to minimize the interference of disturbing factors. The stimulation interval between two stimuli in double-stimulation groups is 60 min [28], which could maximize the long-term potentiation (LTP) of synapses.

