### 2.16. Study Hypothesis

Firstly, UPDRS scores are expected to be significantly lower in group A1 and A2 than in group S1 and S2 after stage 1, and the scores show a trend from low to high in groups A2, A1, S2, and S1 after stage 2. Next, the change in the slope of the weekly UPDRS scores will be compared among the 4 groups. We expect a slower rate of deterioration (i.e., increase in UPDRS scores) with the iTBS intervention than with the pseudo-stimulation group. The mean total UPDRS score deteriorates less from baseline to week 28 in the early-start groups than in the delayed-start groups. For the changes in slope of UPDRS scores between weeks 14 and 28, the early-start groups are expected to respond better than the delayed-start groups.

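### Patients are called blind to treatment, but the sham coil hides only active versus sham; the single-versus-double comparisons are not patient-blind

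*Protocol article*

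**What the plan says.** Section 2.8 of the protocol article states "All the patients are blind to treatment" and rests this on the coil: "Coil replacement will be completed before the patient enters the treatment room, which ensures that subjects are unaware of the grouping". Section 2.9 repeats that the sham coil's matching appearance, sound and vibration keep patients unaware of their group.

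Section 2.2 defines the second design factor: "The only difference between the single- and double-stimulation group is the number of sessions per day". The schedule is given for active and sham stimulation together. In the intensive phase, "The intensive period involves daily or twice-daily iTBS (or pseudo-stimuli) per week, for a total of 10 or 20 sessions"; in the maintenance phase, the figures are "for a total of 24 sessions in the single-stimulation group or 48 in the double group". Section 2.9 adds a feature of the double arms only: "The stimulation interval between two stimuli in double-stimulation groups is 60 min".

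Frequency enters the trial's claims in three places. The primary outcome (2.15) compares UPDRS change across all four groups. The hypothesis in 2.16 orders the arms by frequency as well as by start: "the scores show a trend from low to high in groups A2, A1, S2, and S1 after stage 2". The sample size in 2.17 assumes reductions of 4 (A1), 5 (A2), 2 (S1) and 4 (S2) points.

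**The concern.** The trial has two factors, early or delayed start and one or two sessions a day, and the coil masks only the first. A patient can count sessions from the first treatment day and so knows whether they belong to the pair A1/S1 or the pair A2/S2. Being unaware of the grouping is thus a property the design does not have for frequency.

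If patients expect more sessions to help more, that expectation goes in the same direction as the hypothesised advantage of A2 over A1 and of S2 over S1. The difference between arms would then mix expectation with any effect of the second session. Most exposed are PDQ-39, PSQI, the self-administered side-effect scale and the UPDRS parts that rely on the patient's account. Without a correction, a frequency difference could be read with the authority of a double-blind result.

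**Working it through.** **1. Is frequency observable?** Sessions per 14-week stage, from 2.2:
- single arms: 10 + 24 = 34
- double arms: 20 + 48 = 68

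Over both stages this is 68 against 136. The totals apply to sham as well as active stimulation, so they leave no room for a dummy second session in A1 or S1. The 60-minute interval belongs to the double arms only.

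**2. What each contrast hides from the patient**

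| Contrast | Session count differs? | Patient-blind? |
|---|---|---|
| A1 vs S1, A2 vs S2 (weeks 14 and 28) | no | yes, to active/sham and to early/delayed start |
| {A1, A2} vs {S1, S2} | balanced by 1:1:1:1 allocation | yes, to the factor compared |
| A2 vs A1, S2 vs S1 | yes | no |

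**3. The plan's own figure.** Inputs from 2.17: reductions 4, 5, 2, 4; SD 2; α = 0.05; power 0.9. For a one-way four-group F test the mean is 3.75, and the squared deviations sum to 0.0625 + 1.5625 + 3.0625 + 0.0625 = 4.75. The noncentrality is n × 4.75 / 2². At n = 13 it is 15.44 and power is 0.901; at n = 12 power is 0.872. So 13 per group is reproduced, and 13 / 0.9 = 14.4 rounds up to 15 per group, 60 in total.

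**4. How far the sample size leans on frequency.** The assumed frequency differences are A2 − A1 = 5 − 4 = 1 and S2 − S1 = 4 − 2 = 2. With no frequency effect (4, 4, 2, 2) the noncentrality is 13 × 4 / 4 = 13 and power is 0.840. Frequency contributes to the planned power but does not carry it.

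**5. What an expectation effect could do.** The documents give no size, so the range below is an assumption. With no true frequency effect, SD 2 and 13 per arm, SE = 2 × √(2/13) = 0.78. For a two-sided t test with 24 degrees of freedom:

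| Assumed expectation effect (points) | Effect / SE | Probability of p < 0.05 |
|---|---|---|
| 0 | 0 | 0.05 |
| 0.5 | 0.64 | 0.09 |
| 1 | 1.27 | 0.23 |
| 1.5 | 1.91 | 0.45 |
| 2 | 2.55 | 0.69 |

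An effect of 1 point would equal the whole assumed A2 − A1 difference.

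**6. Can week 14 help?** S1 and S2 have then received only sham, so S2 − S1 reflects session number without active stimulation (SE 0.78). The contrast (A2 − S2) − (A1 − S1) removes an expectation effect that is equal in active and sham arms. Its SE is 2 × √(4/13) = 1.11, which is √2 = 1.41 times larger. With 48 degrees of freedom its power is about 0.14 for a true 1-point effect and 0.42 for 2 points.

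**The case against.** The strongest reply is that the blinding sentence, read with the description of the coil that follows it, means blind to active versus sham, and that this holds. That is a fair reading of the intent. But the same section and 2.9 also say that patients are unaware of their group, and with four groups separated partly by session count this is not so.

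A reader might infer that the frequency comparisons are simply open-label. The documents do not support that. Section 2.8 has clinical assessments scored from coded video by specialists outside the intervention and grouping, and 2.14 has motor assessments scored by two independent physicians. For those items the comparison is assessor-blind; what remains is the patient's own expectation or effort.

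A reader might also infer that patient blinding survives only in stage 1, or that the main neuroprotection comparison is compromised. Neither follows. Knowing one's session count says nothing about whether stage 1 was sham, so A1 vs S1 and A2 vs S2 stay masked at week 28, and the pooled early-versus-delayed contrast is balanced on frequency.

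Three further objections stand in part:
- The study aims do not mention frequency, and 2.17 names no A2 vs A1 or S2 vs S1 test. That such a difference would be reported as double-blind evidence is a risk, not a stated plan. The ranking in 2.16 and the four-group primary outcome still put frequency among the trial's claims.
- What patients are told about the other schedule is not shown. The end-of-trial guess of group assignment suggests that they know of the groups, but not what they expect from them.
- Week 14 is already in the planned repeated-measures ANOVA, so the sham-only data are not ignored. A contrast aimed at expectation would be a new use of them.

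**Conclusion.** The concern holds for patient blinding to frequency. The article claims a masking that its design does not provide for A2 vs A1 and S2 vs S1, where arms differ by 34 against 68 observable sessions per stage. This follows from the schedule alone. The consequence is conditional: an expectation effect of 0.5 to 2 points, which is an assumed range, would raise the chance of a significant pairwise frequency difference from 0.05 to between 0.09 and 0.69 at SD 2 and 13 per arm. The upper values are more plausible for scores that rest on the patient's report than for masked video ratings.

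The early-versus-delayed contrasts at weeks 14 and 28 are not affected, and no change in sample size follows. The point should be corrected because it limits what can be concluded about double versus single iTBS.

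**What to change.** 1. In 2.8 and 2.9, state that patients are blind to active versus sham stimulation and to early versus delayed start, but not to the number of daily sessions.
2. In 2.16 and 2.17, base double-blind conclusions at weeks 14 and 28 on A1 − S1 and A2 − S2, or on the pooled, frequency-balanced contrast of early with delayed start.
3. Report A2 − A1 and S2 − S1 as not patient-blind. Rest their interpretation on the masked video-rated motor scores, and add a caution for patient-reported scales and the patient-reported parts of UPDRS.
4. Use the week-14 sham-only difference S2 − S1, or (A2 − S2) − (A1 − S1), only as a supportive check on expectation. State its limits: the four-arm contrast has SE 1.11 against 0.78, it assumes equal expectation in active and sham arms, and it addresses week 14 while the ranking in 2.16 is after stage 2.

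The cost is protocol wording and some analysis work, with no new data or patients. The downside is a weaker claim about double versus single iTBS.

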### 2.9. iTBS Intervention and Follow-Up

During iTBS, three consecutive 50 Hz pulses are embedded in 5 Hz pulses (200 ms interval). The pattern is then repeated every 10 s in 2 s stimuli followed by 8 s rest sequence, for a total of 600 pulses in each session. In this study, the NS5000 transcranial magnetic stimulator and accompanying devices manufactured by Wuhan Yiruide New Technology Ltd. are used for treatment and measurements. Like the placebo control group in drug experiments, the pseudo-stimuli group is the control group to the active iTBS group. Active and pseudo-stimuli are delivered by matched coils, and a special pseudo-stimuli coil with the same appearance and sound as the active coil will be used. Patients can hear the specially designed sound and feel the vibration during stimulation, but there is no actual stimulation effect. This ensures that subjects are unaware of the grouping. Based on previous results, iTBS intervention was well tolerated with only few subjects reporting discomfort or pain, and no pathological increases in cortical excitability or seizure activity recorded on EEG/EMG monitoring [24,25,26].

Throughout the intervention, patients are first instructed to sit stably and relax in a comfortable position. Before the first intervention, each patient’s resting motor threshold (RMT) should be measured, which is defined as the minimum stimulus intensity necessary to elicit an overt motor response in the abductor pollicis brevis for ≥50% of applied stimuli [27]. We deliver iTBS to the bilateral primary motor cortex (M1) at 100% RMT. Stimulation targets for bilateral M1 are localized according to individual MRI brain structure images under the visor2 ^TM^ neuro-navigated system (ANT Neuro Ltd., Hengrlo, The Netherlands). Subjects in each arm undergo two intervention circles, each composed in an intensive phase for 2 weeks, followed by a maintenance phase of twice-weekly sessions for 12 weeks. Each patient should be stimulated at the same time of day to minimize the interference of disturbing factors. The stimulation interval between two stimuli in double-stimulation groups is 60 min [28], which could maximize the long-term potentiation (LTP) of synapses.

### 2.10. Paired Pulse TMS (ppTMS) Strategy

Paired-pulse transcranial magnetic stimulation (ppTMS) is a non-invasive method utilized to measure GABAergic activity within M1 to probe inhibitory and excitatory networks, which is a common TMS-combined test that allows for quick and easy measurements before and after treatment [29,30]. Before having iTBS, we use a paired-pulse TMS (ppTMS) strategy to investigate intracortical inhibitory and excitatory functional connections within M1, including short-interval intracortical inhibition (SICI), long-interval intra-cortical inhibition (LICI), and intracortical facilitation (ICF) [31]. To conduct ppTMS, a hand-held figure-of-eight coil and NS5000 transcranial magnetic stimulator are used (Wuhan Yiruide New Technology Ltd., Wuhan, China). After pre-test resting EEG, RMT of each subject will be tested, which is the minimum stimulus intensity triggered by TMS pulse in right M1 evoking at least five responses (above 50 μV) out of 10 stimuli. Motor-evoked potential (MEP) can be elicited by ipsilateral M1 stimulus and obtained using surface EMG recording electrodes settled on contralateral hand. SICI and ICF are assessed through ppTMS with a subthreshold conditioning stimulus (CS) at 80% of RMT followed by a suprathreshold testing stimulus (TS) at 120% of RMT according to standard protocols [32,33]. The interstimulus interval (ISI) between the CS and TS determines whether the cortex produces inhibitory or excitatory activity [34]. In most cases, SICI attenuates the MEP response when a subthreshold CS precedes a suprathreshold TS by 1–6 ms, while ICF facilitates the MEP response when a subthreshold CS precedes a suprathreshold TS by 8–30 ms [32,35]; thus, our experiment adopts ISI = 5 ms and ISI = 20 ms for SICI and ICF measurement, respectively. Additionally, LICI is typically tested by applying suprathreshold CS at 120% of RMT followed by TS at 120% of RMT at ISI = 200 ms, resulting in a reduced MEP amplitude [31]. All the measurements will be performed first in the more affected hemisphere and then in the less affected hemisphere.

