### 2.12. Electroencephalogram (EEG) and Electromyographic (EMG)

Resting EEG signals are received using EBneuro Beplus pro EEG 64-channel recording system (EBneuro, Florence, Italy) in a separate, quiet room. Sixty-four-channel EEG signals are sampled at a frequency of 1024 Hz, and a 50 Hz notch filter is applied to reduce the input noise. The individuals are instructed to seat comfortably in a stable chair with both hands relaxed during the recordings. The skin is cleaned at the electrode contacts with alcohol before attaching the 64-channel-customized EEG cap to reduce skin impedance. The distribution of the electrode gel is applied and adjusted with a flat syringe and cotton swab until all electrodes reach the desired impedance (<10 kΩ). Two sessions of resting EEG will be performed before and after the iTBS stimulus, which consist of 5 min of open eyes and 5 min of closed eyes. With 9 mm-diameter surface electrode patches, EMG traces will be acquired bilaterally from the abductor pollicis brevis (APB) muscles. EMG acquisition will be performed through the EMG module that affiliates to the iTBS stimulator. EEG and EMG measurements will be collected at baseline, week 2, midterm (week 14), week 16, and endpoint (week 28).

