### 2.15. Outcome Measures

According to the results of previous large delayed-start design disease-modifying drug studies, the neuroprotective effect can be commonly reflected by the difference in the changes in the UPDRS score before and after treatment between groups [22,39]. In an NET-PD study, the primary outcome is the differences in changes in UPDRS scores in the four groups before and after the iTBS intervention. As a secondary outcome, we will evaluate the effects of iTBS treatment on clinical symptoms, motor symptoms such as gaiting and postural balance, and non-motor symptoms such as mood, cognition, olfaction, and sleeping condition in PD patients. As a neuro-modulation intervention study, EEG, EMG and MRI images can also be visualized to indicate the functional activity status of the brain. The safety of the treatment will be assessed using a self-administered side effect scale. Additionally, self-administered side effects scales will be used to assess iTBS safety.

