### 2.17. Sample Size and Statistical Analysis

With reference to data from previous studies published in relevant journals, a total of 60 PD patients are proposed to be enrolled in this single center study. The sample size of this study was calculated based on the improvement in the UPDRS scale after 28 weeks of treatment and differences between groups. Calculations are performed using PASS (Power Analysis and Sample Size) 2008 software (UT, OH, USA), assuming a four-point reduction in the UPDRS at the end of treatment in A1, a five-point reduction in A2, a two-point reduction in S1, and a four-point reduction in S2, with a standard deviation of 2, a test level of 0.05, and a degree of certainty of 0.9 yielded for 13 subjects per group. Considering that the patient dropout rate may be about 10% [24,40], the final plan is to enroll n = 15 cases in each group for n = 60 cases in total. The minimum sample size required to meet the hypothesis of this clinical study is 60, and actual samples of 60 cases or more are in accordance with the clinical study design principles and statistical requirements.

Statistical analysis applies SPSS 20.0 for processing; MRI, EEG, and EMG data are processed on MATLAB platform (Math Works Inc., Natick, MA, USA). All statistics are performed using two-sided tests, and α = 0.05 is the cut-off point used to decide whether the hypothesis is statistically significant. Between-group comparisons of quantitative data will be performed using analysis of variance (ANOVA) or Wilcoxon rank sum test depending on the distribution of the data. A paired *t*-test or Wilcoxon signed-rank test will be used for comparison before and after treatment. Categorical data are tested by chi-square test or exact probability method (if the chi-square test is not applicable).

To compare the changes in UPDRS scores before and after the iTBS intervention at each time point, mainly comparing the differences in their means, two-way repeated-measures ANOVA was used to compare the main effects and the interaction effects between the two for different groups and follow-up points (baseline, week 14, week 28), and post hoc analysis was performed using the Bonferroni test to compare the differences between each follow-up point and baseline scores.

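### Section 2.10 takes the paired-pulse motor threshold from right M1 but applies it to measurements in both hemispheres

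*Protocol article*

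**What the plan says.** All of the relevant text is in the protocol article, mostly in section 2.10.

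- **Threshold.** The RMT of each subject is "the minimum stimulus intensity triggered by TMS pulse in right M1 evoking at least five responses", counted out of 10 stimuli with responses above 50 μV.
- **SICI and ICF.** These use a "subthreshold conditioning stimulus (CS) at 80% of RMT followed by a suprathreshold testing stimulus (TS) at 120% of RMT".
- **LICI.** This is described as "applying suprathreshold CS at 120% of RMT followed by TS at 120% of RMT at ISI = 200 ms".
- **Sides tested.** The section closes with "All the measurements will be performed first in the more affected hemisphere and then in the less affected hemisphere".
- **Recording.** The MEP "can be elicited by ipsilateral M1 stimulus and obtained using surface EMG recording electrodes settled on contralateral hand", with no side named. Section 2.12 adds that "EMG traces will be acquired bilaterally from the abductor pollicis brevis (APB) muscles".

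Section 2.9 gives a separate RMT for setting the treatment dose. It names no hemisphere and does not refer to the paired-pulse measurements. No section gives a left-sided or hemisphere-specific RMT for paired-pulse TMS.

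**The concern.** SICI and ICF depend on a conditioning pulse below, and a test pulse above, the threshold of the cortex being stimulated. LICI depends on both pulses being above it. The percentages in section 2.10 therefore have their intended meaning only relative to the hemisphere under test. If the threshold comes from right M1 and is carried over to the left, left-hemisphere pulses miss the intended percentages by an amount that differs between patients.

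What is at stake is the precision of a mechanistic measure. Section 2.1 lists exploring mechanism among the aims. Section 2.15 gives the electrophysiology a descriptive role: "EEG, EMG and MRI images can also be visualized to indicate the functional activity status of the brain". The primary outcome is change in UPDRS, and it does not depend on this threshold.

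**Working it through.** The plan states no figure to reproduce, so the check sets the sentences against each other and then asks what the literal reading would do to the pulses.

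**Consistency of the text**

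1. The RMT sentence names one site, right M1.
2. The intensity sentences refer to RMT without naming a side.
3. The last sentence requires measurement on both sides, ordered by how affected the hemisphere is.
4. The inclusion criteria in section 2.3 do not select patients by side, so right M1 cannot stand for the more affected hemisphere in every patient.

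Two readings remain:

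- **Literal.** The RMT is not among the measurements covered by the last sentence. Left-hemisphere pulses are then scaled to the right hemisphere's threshold.
- **Drafting slip.** The RMT is among those measurements and is taken on both sides. The words right M1 then contradict the last sentence.

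**Size on the literal reading**

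Inputs: 80% (SICI/ICF conditioning pulse) and 120% (SICI/ICF test pulse and both LICI pulses), from section 2.10; 60 patients, from section 2.17. Let r = left RMT / right RMT. The article does not give r.

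Intensity delivered, as a percentage of the left threshold = stated percentage / r.

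Break-even values, which use only the stated percentages:

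- 80 / 0.80 = 100. At r = 0.80 the conditioning pulse reaches the left threshold.
- 120 / 1.20 = 100. At r = 1.20 the SICI/ICF test pulse and both LICI pulses fall to the left threshold.

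So the intended status holds for 0.80 < r < 1.20. Within those limits the intensity still shifts. The values of r below are assumptions, chosen to show a range:

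| Assumed r | Conditioning pulse (80 / r) | Test pulse and both LICI pulses (120 / r) |
|---|---|---|
| 0.85 | 94.1% | 141.2% |
| 0.90 | 88.9% | 133.3% |
| 0.95 | 84.2% | 126.3% |
| 1.00 | 80.0% | 120.0% |
| 1.05 | 76.2% | 114.3% |
| 1.10 | 72.7% | 109.1% |
| 1.15 | 69.6% | 104.3% |

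Hemispheres concerned: 60 × 1 = 60 left hemispheres out of 60 × 2 = 120 measured. On the drafting-slip reading the number is 0.

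**Effect on the planned comparisons**

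The wording is the same in all four arms, so it does not favour any of them. For before-and-after comparisons section 2.17 says that a paired t-test or "Wilcoxon signed-rank test will be used for comparison before and after treatment". Within a patient, a side difference that stays stable between visits is largely shared by the two measurements. The article plans no comparison of paired-pulse results between hemispheres, so none is harmed.

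**The case against.** The strongest reply is that the harmful reading is the less likely one. The RMT test is described in the same section whose last sentence covers all measurements. The MEP sentence is neutral as to side, and EMG is recorded from both hands. The text never says that only one RMT is taken or that it is carried across to the other hemisphere. On this view right M1 is a stray phrase, no hemisphere is affected, and only an edit remains.

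The size is also conditional. The side differences in the table are assumed, and across the whole range from 0.85 to 1.15 the conditioning pulse stays below threshold and the other pulses stay above it. SICI, ICF and LICI are not named among the outcomes in section 2.15 or in the analyses in section 2.17.

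Most of this stands, and it limits the point to a minor one. Cross-hemisphere scaling is a possibility and is not shown to be the practice. The objection does not remove the conflict, however. The article names a side, and that side does not fit its own two-sided measurement plan. This is a stated operating rule that is wrong or contradictory, which differs from detail left to a fuller document. An operator who followed the sentence as written would set left-hemisphere pulses from the other side.

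**Conclusion.** The concern holds, as a minor point. The RMT sentence in section 2.10 is wrong on either reading: it sets the left hemisphere's pulses from the right hemisphere's threshold, or it contradicts the sentence that orders testing on both sides.

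The actual size cannot be determined from the article. It is zero if the wording is a slip or if the two thresholds are equal. On the literal reading, the departure from the intended percentages grows with the side difference, and the pulses lose their intended status once r reaches 0.80 or 1.20. Nothing in the article shows how close patients come to those limits. The consequence would be extra noise in an exploratory measure. The UPDRS comparison, the sample size and the primary analysis are unaffected.

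**What to change.** In section 2.10, replace right M1 with the M1 being tested. Add one sentence stating that the conditioning and test pulses for each hemisphere are set from that hemisphere's own RMT.

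If thresholds are already taken on both sides, this is only a wording change. If a single right-sided threshold is in use, it also costs a few extra minutes per paired-pulse session for a second threshold. It needs no new equipment, because EMG is already recorded from both hands. Section 3 reports two patients enrolled when the article was written, so at that date 60 − 2 = 58 of the planned patients could have been measured under the corrected wording. The number still to benefit now depends on current enrolment.
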